**Fig 1 pone.0306394.g001:**
[figure not shown]
SPIRIT timeline: Schedule of enrolment, intervention, and assessment for both study groups at four different time points T1 -T4.

### Study procedures

Standardised questionnaires will be used at all three centres to ensure uniformity in the data collection. Additionally, translations and assistance in completing the questionnaires in the local languages (Hindi, Gujarati, and Marathi) will be provided to those who require them by a trained member of the research team.

#### Anthropometric and socio-demographic

During baseline assessment, participants will be requested to provide self-reported data on sociodemographic variables, including age, gender, education, and marital status, as well as anthropometric measurements such as height and weight. Detailed instructions on the precautions to be taken while measuring weight will be provided to ensure the accuracy of the self-reported data (S1 Appendix). The data will be reported as the average of three readings. Body mass index (BMI) will be calculated.

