## Methods

### Design

The present study is a prospective, open-label, matched control trial. Ethical approval for the study was granted by the Institutional Ethics Committee (IEC) (Ref. no. FFDRF/IEC/2023/3). The trial is prospectively registered with the Clinical Trials Registry-India (CTRI) (Ref. No. CTRI/2023/06/053885) (S1 File). This study will adhere to the standards for clinical research outlined in the Declaration of Helsinki. The protocol is designed according to the SPIRIT guidelines (S1 Checklist).

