### Outcome measures

The primary outcome measures are a) Weight loss of more than or equal to 10% and b) Remission of T2D (HbA1c less than 6.5% for at least 3 months without medication). Secondary outcomes include a) reduction in dosage and/ or frequency/ class of drug or complete stoppage of diabetes medication, b) improved glycemic control (HbA1c less than 7% with or without medication), c) reduction in fasting glucose levels (below 126 mg/dl) and PP blood glucose levels (below 200 mg/dl) with or without glucose-lowering medications), d) improvement in diabetes-related complications (nephropathy- improvement in terms of eGFR>90 mL/min/1.73m^2^), e) improvement in comorbidities (hypertension- blood pressure ≤140/90 and dyslipidaemia- Total cholesterol <200 mg/dl, triglycerides <150 mg/dl, and HDL >40 mg/dl for males and >50 mg/dl for females), and f) improvement in mental health outcomes (anxiety and depression- Reduction in the score—below 10).

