In this context, this study aims to contribute to the growing body of evidence supporting the effectiveness of holistic interventions in managing T2D, particularly in diverse populations, such as those in India. By addressing not only physical health, but also mental well-being and cultural considerations, our findings may pave the way for more tailored and effective diabetes management strategies globally.

Our study has a few limitations that should be considered. First, the socioeconomic status of the participants may limit the generalisability of our findings to the broader Indian context because our online diabetes management program operates on a subscription-based model that may restrict access to those who can afford it. Future trials adopting a randomised-controlled design may be planned based on the outcome of the present study to address this. Second, the study relies on self-reported parameters, such as anthropometry, which may be subject to data errors despite detailed instructions and regular monitoring of incoming data. Additionally, although our study is not a true randomised controlled trial, we have chosen a matched-control group for our intervention group which is more acceptable in a real-world setting. Finally, due to the comprehensive nature of our planned intervention, we will not be able to examine the impact of individual components. Notwithstanding these limitations, we believe that our research will provide valuable insights into the effectiveness of our holistic diabetes management program.

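### The co-primary 10% weight-loss outcome relies on self-reported weight in an open-label, non-randomised trial, and the stated safeguards do not address modest misreporting that differs between groups

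*Protocol article*

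**What the plan says.** All places are in the protocol article.

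- **Design:** the study is a "prospective, open-label, matched control trial". The Discussion adds that it is not a true randomised trial.
- **Outcome measures:** the first primary outcome is "Weight loss of more than or equal to 10" per cent. The second is remission.
- **Anthropometric and socio-demographic:** at baseline, "participants will be requested to provide self-reported data on sociodemographic variables, including age, gender, education, and marital status, as well as anthropometric measurements", which include height and weight. Two safeguards follow. The first is weighing instructions (in an appendix not shown here): "Detailed instructions on the precautions to be taken while measuring weight will be provided to ensure the accuracy of the self-reported data". The second is averaging: "The data will be reported as the average of three readings".
- **Discussion, limitations:** "the study relies on self-reported parameters, such as anthropometry, which may be subject to data errors", in spite of the instructions and of regular monitoring of incoming data. This statement is not confined to baseline.
- **Statistical analyses:** values beyond 3 SD are cross-checked and, failing correction, treated as missing.
- **Intervention and Mode of delivery:** moving to the next phase depends on meeting the previous phase's target, a target BMI is set, and participants enter their weight in an app shared with their team. Delivery is online.
- **Control group:** routine care with education. No weight-reporting procedure is described.
- **Biochemical:** HbA1c comes from accredited laboratory reports.

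**The concern.** A yes/no outcome at a fixed threshold is sensitive to a small systematic shift, because some participants always lie just below the cut-off. Here the person who supplies the number knows the group. In the intervention group that person has also worked towards a weight target and reported to a coaching team. Under-reporting at follow-up, or over-reporting at baseline, would inflate apparent loss in the group the trial hopes will do better.

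The stated safeguards act on other kinds of error. Instructions and the mean of three readings reduce random error. Monitoring of incoming data looks at the self-reports themselves. The 3 SD check catches gross errors. The limitations paragraph speaks of data errors, not of reporting that differs between unblinded groups. HbA1c has an independent source and weight does not, so the two co-primary outcomes are unequally protected.

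**Working it through.** The article gives no figure for misreporting, so there is none to reproduce. Body weight, mean loss, SD and the size of misreporting below are all assumptions.

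**1. Shift in the responder rate in one group**

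Let percentage loss be Normal(m, s). The responder rate is 1 − Φ((10 − m)/s). Under-reporting by 1 kg at 12 months, with a 75 kg baseline, adds 100/75 = 1.33 points to each participant's percentage loss.

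| m, s | True rate | Reported rate | Difference (points) |
|---|---|---|---|
| 6, 7 | 28.4% | 35.2% | 6.8 |
| 6, 5 | 21.2% | 29.7% | 8.5 |
| 8, 6 | 36.9% | 45.6% | 8.6 |
| 10, 5 | 50.0% | 60.5% | 10.5 |
| 12, 7 | 61.2% | 68.3% | 7.1 |

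For m = 8, s = 6 the rates are 1 − Φ(0.333) = 36.9% and 1 − Φ(0.111) = 45.6%. Over m = 6, 8, 10, 12 and s = 5, 6, 7 the difference runs from 6.8 to 10.5 points.

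**2. Would the outlier check see it?**

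If it is applied to percentage loss with an SD of 5 to 7, the limit lies 15 to 21 points from the mean. A shift of 1.33 points would rarely trigger it.

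**3. No true effect**

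Take 132 per group (the stated requirement for weight) and two-sided 0.025 (the per-outcome level in the sample size section), so z = 2.24. The chance of a significant result is approximately

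Φ{[p1 − p0 − 2.24·√(2p̄(1 − p̄)/n)] / √[(p1(1 − p1) + p0(1 − p0))/n]}.

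With 80 kg, mean loss 5% and SD 6 in both groups, p0 = 20.2%:

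| Under-report, one group | p1 | Chance of a significant result |
|---|---|---|
| 1 kg (1.25 points) | 26.6% | about 15% |
| 2 kg (2.5 points) | 33.8% | about 60% |
| 3 kg (3.75 points) | 41.7% | about 94% |

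The nominal level is 2.5%. Over 70 to 90 kg, mean 3 to 8% and SD 5 to 8, the range is 7 to 34% at 1 kg, 27 to 93% at 2 kg, and 59% to over 99% at 3 kg.

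**4. A large reported effect**

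Suppose the intervention group reports mean 8%, SD 6 (36.9% responders). Controls lose a mean of 0 to 3% with SD 4 to 6 (0.6 to 12.2% responders). Completers number 180 × 0.70 = 126 per group. Using z = (p1 − p0)/√(2p̄(1 − p̄)/n):

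- Removing 1 kg (75 kg baseline) lowers the mean to 6.67% and the rate to 28.9%; z is 3.3 to 6.3.
- Removing 1.5 kg lowers the mean to 6% and the rate to 25.2%; z is 2.7 to 5.8.

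All exceed 2.24, so the result survives.

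**5. A weaker reported effect**

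With a reported mean of 6%, SD 6 (25.2%) against 12.2% in controls, z = 2.66, which is significant. Removing 1 kg gives 18.7% and z = 1.44, which is not. Against controls at 0.6%, the same correction leaves z = 4.9.

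**The case against.** The strongest reply is that the sponsor has already disclosed the reliance on self-report, monitors incoming data and cross-checks outliers. Self-report is also a pragmatic choice for an online programme. This narrows the point but does not remove it: neither safeguard is an independent weighing, neither would notice a 1 kg shift, and the disclosure does not mention differential reporting.

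Several stronger readings are tempting, and the documents do not support them.

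- *A significant weight result could not be told apart from reporting behaviour.* Step 4 shows otherwise: a large difference survives the removal of 1 to 1.5 kg. The high false-positive figures in step 3 need no true effect and a uniform shift of 2 to 3 kg.
- *The article states that follow-up weights are self-reported.* It says so explicitly only for baseline. For 12 and 18 months this is an inference, though a likely one.
- *Controls have no weight goals and are never weighed by staff.* The article does not say. They attend clinics and receive education, and only the absence of a described matching procedure can be stated.
- *The app entries are the trial's outcome data.* The article describes the logging but does not say that these entries are the outcome data.
- *No planned analysis addresses the problem.* This can be said only of the article, since a separate analysis plan may exist.

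It also stands that no figure in the documents fixes the direction or size of misreporting, and that remission is less exposed because HbA1c is measured in laboratories.

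**Conclusion.** The concern holds in a conditional form. One co-primary outcome relies on self-reported weight where group is known, where the incentives described for the intervention group have no described counterpart among controls, and where the stated safeguards are aimed at another kind of error. Under the assumptions of step 1, 1 kg of one-sided under-reporting is worth about 7 to 10.5 percentage points of responders. That is enough to create or inflate a difference when the true effect is small, and not enough to overturn a large one. It should be dealt with because the remedy is cheap, but it is not fatal to the trial.

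**What to change.** At 12 and 18 months, and at baseline for anyone not yet enrolled, ask participants in both groups to upload time-stamped photographs of the scale display for the three readings already required, using the same scale each time. State explicitly how follow-up weight is obtained in each group.

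Use the photographed readings for the weight outcome. If a self-report is kept where a photograph is missing, flag it, because it lets some of the suspected bias back in. Report a sensitivity analysis restricted to photographed weights.

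Add a tipping-point analysis that adds 0.5, 1.0, 1.5 kg and more to the intervention group's 12-month weights and reports where significance is lost. It needs no new data, and it would help the sponsor if the effect is large.

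The cost is a small burden on participants, a short procedure note and some missing photographs, with no extra visit or assessor. Two limits remain. Recruitment began on 1 March 2024, so baselines of those already enrolled stay unverified. And a photograph makes a reading checkable without excluding every form of manipulation, such as who stood on the scale.

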#### Biochemical

Data on the following biochemical tests will be collected from lab reports done at Government certified- NABL (National Accreditation Board for Testing and Calibration Laboratories, Govt. of India) labs; Primary: HbA1c, fasting blood sugar (FBS), postprandial blood sugar; secondary: lipid profile (total cholesterol, HDL, LDL, and VLDL), thyroid profile (thyroid-stimulating hormone), fasting insulin, serum creatinine levels, eGFR, urine microalbumin, liver function parameters, high sensitivity C-reactive protein (hs-CRP), C-peptide, Vitamin D, and Vitamin B12 will be collected based on availability in the submitted reports. Homeostatic model assessment of insulin resistance (HOMA-IR) and homeostatic model assessment of beta cell function (HOMA-B) will be calculated using standard formulas to assess insulin resistance and beta-cell function, respectively [19].

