### Setting and eligibility criteria

The proposed study will be conducted at the Freedom from Diabetes Clinic, which operates on an online subscription-based model of 1-year duration for the management of diabetes (intervention group). Additionally, the study will include participants from two private clinics in Pune and Ahmedabad (India) (Control Group), which provide standard medical care based on established guidelines for individuals with diabetes. All individuals with T2D who enrol in these centres between March and August 2024 and meet the eligibility criteria will be recruited for this study Table 1.

**Table 1 pone.0306394.t001:** Eligibility criteria for the DiRemI study.

Inclusion Criteria	Exclusion Criteria
Age between 30 and 70 years	Pancreatitis or drug-induced diabetes (Steroids)
Confirmed diagnosis of type 2 diabetes, which may be managed with oral hypoglycemic agents, insulin, Ayurvedic antidiabetic medications, or have an HbA1c level of ≥ 48 mmol/mol (6.5%) with or without medication	Other types of diabetes (type 1 diabetes mellitus, diabetes insipidus, maturity-onset diabetes of the young, latent autoimmune diabetes in adults, or Gestational Diabetes)
Body mass index (BMI) between 25 kg/m^2^ and 35 kg/m^2^	Advanced complications related to nephropathy (eGFR<30 mL/min/1.73 m^2^, urine microalbumin >1000 mg), retinopathy (severe non-proliferative diabetic retinopathy and proliferative diabetic retinopathy), neuropathy (peripheral artery disease or diabetic neuropathy resulting in complete numbness and loss of sensation, amputations, ulcers, foot deformities, Charcot’s foot)
Duration of type 2 diabetes less than 15 years	History of heart attack, cardiac arrhythmia, bypass or stent placement surgery, ischemic heart disease, angina (class II or III), myocardial infarction within the previous 6 months, reported ejection fraction <40%, abnormal ECG, and positive stress test results (moderate or severe)
Ready to provide written informed consent	Known history of cancer
Agree to undergo the examination, lifestyle intervention program, and post-program evaluation	Pregnant and lactating women
Well-oriented in time, space, and as a person	Patients who have required hospitalization for any diabetes-related complications in the last 6 months or for depression or are on antipsychotic drugs

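### eGFR is taken from submitted laboratory reports with no common equation, although the inputs to compute it are collected; if equations differ between groups or visits, the secondary eGFR >90 outcome can differ at identical creatinine

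*Protocol article*

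**What the plan says.** In the protocol article, the Biochemical section describes where the laboratory values come from: "Data on the following biochemical tests will be collected from lab reports done at Government certified- NABL" laboratories. The secondary items listed there include "fasting insulin, serum creatinine levels, eGFR, urine microalbumin, liver function parameters", and they "will be collected based on availability in the submitted reports". The section then names the indices that the study derives itself: HOMA-IR, and "homeostatic model assessment of beta cell function (HOMA-B) will be calculated using standard formulas". eGFR is not among them, and no eGFR equation is named.

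The inputs for a common calculation are planned. Creatinine is in the same list as eGFR, and the Anthropometric and socio-demographic section collects "self-reported data on sociodemographic variables, including age, gender, education, and marital status".

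Under Outcome measures, the one complication outcome is nephropathy, with "improvement in terms of eGFR>90 mL/min/1.73m^2" as its criterion. The intervention group comes from one online subscription programme, and the controls from "two private clinics in Pune and Ahmedabad (India) (Control Group"). The Statistical analyses section offers optional adjustment for baseline value, age, gender and disease duration. Laboratory and centre are not named there.

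**The concern.** eGFR is not measured. It is calculated from creatinine, age and sex, and different equations give different answers for the same person. A value read from a report carries whichever equation that laboratory uses. With a hard cut at 90, the choice of equation can decide whether a participant meets the outcome.

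This matters more here than in a randomised trial, because group and place of care coincide. If laboratories follow place of care, an equation difference between laboratories would look like a difference between the programme and routine care. A participant who changes laboratory between visits could also cross 90 with unchanged creatinine. Finally, a report that gives creatinine but no eGFR supplies no eGFR under the availability condition, although the value could be computed.

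**Working it through.** The article gives no expected proportion, power or sample size for the eGFR outcome, so there is no figure of the plan to reproduce. The check asks how far the equation alone can move the outcome.

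**Inputs from the article:** the cut at 90; age range 30 to 70; 180 per group enrolled and 132 per group before the dropout allowance.

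**Assumed, because the article does not give them:** three candidate equations, without a race term; mean age 52 (SD 9, limited to 30–70); 40% women; log-normal creatinine with log SD 0.18; three settings of median creatinine.

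**Step 1. Equations** (S = creatinine in mg/dl, A = age in years; κ = 0.9 for men, 0.7 for women)

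- MDRD: 175 × S^(−1.154) × A^(−0.203), × 0.742 for women
- CKD-EPI 2009: 141 × min(S/κ, 1)^α × max(S/κ, 1)^(−1.209) × 0.993^A, × 1.018 for women; α = −0.411 for men, −0.329 for women
- CKD-EPI 2021: 142 × min(S/κ, 1)^α × max(S/κ, 1)^(−1.200) × 0.9938^A, × 1.012 for women; α = −0.302 for men, −0.241 for women

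For a man of 50 with S = 0.90, S/κ = 1, so the min and max terms drop out:

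- MDRD: 175 × 1.129 × 0.452 = 89.3
- CKD-EPI 2009: 141 × 0.7038 = 99.2
- CKD-EPI 2021: 142 × 0.7327 = 104.0

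| Participant | MDRD | 2009 | 2021 |
|---|---|---|---|
| Man 50, 0.90 | 89.3 | 99.2 | 104.0 |
| Man 50, 1.00 | 79.1 | 87.4 | 91.7 |
| Woman 50, 0.70 | 88.6 | 101.0 | 105.3 |
| Woman 60, 0.70 | 85.4 | 94.2 | 98.9 |

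Each row straddles 90.

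**Step 2. Share above 90 at a single visit, same simulated creatinine values**

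| Median creatinine, men/women | MDRD | 2009 | 2021 |
|---|---|---|---|
| 0.80/0.65 | 68.2% | 82.3% | 87.7% |
| 0.90/0.70 | 46.9% | 65.2% | 73.4% |
| 1.00/0.80 | 23.4% | 40.7% | 49.3% |

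**Step 3. Apparent group difference with no true effect.** If a fraction m of one group's reports uses equation B, and all other reports in both groups use equation A, the expected gap is m × (p_B − p_A). With m = 0.30 and the middle setting:

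- MDRD against 2009: 0.30 × 18.3 = 5.5 points
- MDRD against 2021: 0.30 × 26.5 = 8.0 points
- 2009 against 2021: 0.30 × 8.2 = 2.5 points

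Over all three settings the range is 1.6 (0.30 × 5.4) to 8.0, so about 2 to 8 points. If the mix is equal in both groups, the gap is 0.

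The outer bound is one group wholly on MDRD and the other wholly on CKD-EPI 2021. The gap is then about 20 to 27 points, and the chance of p < 0.05 is 97–100% at 132 to 180 per group. For CKD-EPI 2009 against 2021 in the same extreme, it is 5 to 9 points and 24–40%.

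**Step 4. Outcome read as change.** Now define improvement as moving from 90 or below at baseline to above 90, with each participant staying on one equation. Assume 5–8% creatinine variation at each visit, one year of ageing and no true effect, and use the middle setting with log SD 0.18 to 0.22.

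- Among all participants, 3.9–8.8% cross. The equations differ by at most about 1.5 points, and 0.30 × 1.5 = 0.45 points.
- Among those at or below 90 at baseline, the equations differ by about 2 to 9 points, and 0.30 × 2 to 0.30 × 9 = 0.6 to 2.7 points.

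In a rerun with the lower creatinine medians, the all-participant difference reached about 3 points (0.30 × 3 ≈ 1 point). Most of the single-visit gap therefore cancels when the outcome is a change and the laboratory is stable.

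**The case against.** The strongest objection is that this is a derivation rule for a secondary variable. A journal article normally leaves such a rule to the full protocol or the analysis plan, and neither is shown. Naming HOMA as calculated does not exclude calculating eGFR later. Part of this stands: an unseen document could already name an equation. But the article is not silent. It places eGFR with the values read from reports, subject to availability, and lists separately what the study computes. A better method than the one stated is available from data already planned.

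The second objection concerns what the documents do not show, and it stands. A reader might infer that many laboratories are involved, that they differ by group, and that they use different equations. The article says only that accredited laboratories, in the plural, are the source. Online delivery against two city clinics makes a difference in laboratories plausible, but does not establish it. Likewise, that a report with creatinine but no eGFR would be treated as missing follows from the availability condition but is not stated outright.

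The third objection is that the single-visit share above 90 overstates the effect, because the outcome is worded as improvement. This also stands: with a stable laboratory per participant the distortion is much smaller (Step 4). It returns if participants change laboratory between visits in a way that differs by group.

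Finally, eGFR enters neither primary outcome. It affects one of six listed secondary outcomes, in a comparison that already carries the larger limits of a non-randomised design.

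**Conclusion.** The point holds in conditional form. The plan takes a derived quantity from reports without a common equation, although it collects everything needed to derive it uniformly. If equations differ between the groups, or within a participant over time, the eGFR >90 outcome can differ with no difference in creatinine. Creatinine reported without eGFR would add avoidable missing values.

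The size depends on assumptions that the documents cannot settle. It is zero if the mix of equations is the same in both groups. It is up to about 2 to 8 points for the single-visit share above 90 if 30% of one group's reports use another of the three assumed equations. It is smaller for a change from baseline with a stable laboratory.

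A reader might go further and conclude that the outcome is biased, or take the 20-to-27-point extreme as an estimate. The documents do not support either, since they identify neither the laboratories nor the equations. This is a nearly free improvement to a secondary outcome. It does not threaten the trial's main conclusions.

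**What to change.** State in the analysis plan that, for the nephropathy outcome, eGFR will be calculated for all participants at baseline and every later visit. The inputs are reported creatinine, age at that visit and gender, with one equation named before outcome data are compared. Use the calculated value wherever creatinine is available, whether or not the report prints an eGFR, and do not use the printed value for the outcome.

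Confine the change to the outcome analysis. Recruitment began on 1 March 2024 (Trial status), and participants already enrolled should not be reclassified for eligibility on a recalculated value.

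The cost is one sentence and one derivation step, with no new data or visits. The equation-driven gap between groups is then zero by construction. Differences between laboratories in the creatinine assay itself would remain and should be acknowledged when the result is reported.

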#### Medical management

The primary focus of medical management is to closely monitor participants during the intervention. The assigned physician is accountable for evaluating the participant’s health condition at the outset by considering a comprehensive medical history of diabetes, its potential complications, and any co-existing conditions, along with biochemical analysis of the parameters listed previously. Following the correction of micronutrient deficiencies, if any, the physician adjusts the medication dosage according to the participant’s weight, BMI, and daily self-reported blood sugar level (BSL) through the mobile application. Once blood sugar levels are stabilised, participants are asked to report them less frequently (weekly/fortnightly). The physician considers the participant’s history of comorbidities for further management and maintains strict control over the HbA1c levels throughout the year. In addition to daily dosage modifications, the physician is required to conduct at least three medical consultations with the participant throughout the one-year program.

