### Control group (Routine medical care)

The control group will receive routine medical care along with education for management of T2D and its associated comorbidities based on current clinical guidelines.

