The importance of mental health is unparalleled and closely connected to effective T2D management. In addition to dietary and exercise adjustments, this trial encompasses a multifaceted approach to both physical and mental well-being, which has not been extensively addressed in previous studies. Research has demonstrated that participants with T2D who experience depression are twice as likely to exhibit non-adherence to medications for diabetes, blood pressure, and cholesterol when compared to non-depressed participants [37]. Moreover, individuals with poorer diabetes self-care tendencies generally exhibit heightened levels of psychological distress, diminished social support, and decreased self-efficacy [38]. In the proposed trial, T2D participants will receive psychological support from trained psychologists to help address and cope with life stressors and achieve optimal disease management.

Another unique feature of our study is the focus on medical management. Unlike previous studies on ILI [17, 39] that completely withdrew all diabetes medicines before the commencement of the trials, in our study, the physician will ensure systematic tapering of medications based on daily reported blood sugar levels. This approach will ensure appropriate medical management of participants with a longer duration of diabetes and, hence, more complications. Furthermore, medical management will address and correct nutritional deficiencies through supplementation.

Our study differs from many other studies on ILI, which have generally focused on specific population demographics (e.g. younger age and newly diagnosed T2D) [35, 39, 40] and limited interventions targeting specific features, such as low/very low-calorie diets, diet replacement, and weight loss, with less emphasis on physical activity and intensive exercise training [36, 41]. Our study represents a unique approach that incorporates a comprehensive, personalised methodology specifically designed to accommodate the distinct features of each participant, with a particular focus on a demographically varied group of individuals aged between 30 and 70 years, who have been living with diabetes for up to 15 years.

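### HOMA-IR and HOMA-B are planned with no exception for insulin users, in whom measured fasting insulin can include injected insulin, so HOMA-B does not measure beta-cell function

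*Protocol article*

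**What the plan says.** The Biochemical subsection of Methods lists fasting insulin and C-peptide among the secondary tests. These "will be collected based on availability in the submitted reports". It then states that HOMA-IR and HOMA-B "will be calculated using standard formulas to assess insulin resistance and beta-cell function, respectively". The formulas are cited, not printed. No participants are set apart by treatment, and C-peptide is not linked to either index.

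Four other places bear on this:

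- **Table 1 (eligibility)** admits confirmed type 2 diabetes "which may be managed with oral hypoglycemic agents, insulin, Ayurvedic antidiabetic medications". No exclusion criterion removes insulin users.
- **Medical management**, for the intervention group: "the physician adjusts the medication dosage according to the participant’s weight, BMI, and daily self-reported blood sugar level (BSL) through the mobile application". The Discussion adds that "the physician will ensure systematic tapering of medications based on daily reported blood sugar levels".
- **Outcome measures** counts "reduction in dosage and/ or frequency/ class of drug or complete stoppage of diabetes medication" as a secondary outcome. HOMA does not appear among the primary or secondary outcomes.
- **Control group**: "The control group will receive routine medical care along with education for management of T2D". Nothing is said about how doses are handled there.

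**The concern.** HOMA-B is read as beta-cell function because fasting insulin is taken to be the patient's own secretion. In someone who injects insulin, the laboratory value may contain both sources, depending on the assay and on when the last injection was given. The index then credits injected insulin to the beta cell. HOMA-IR uses the same insulin value and inherits the problem, although its direction is less predictable.

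This matters because the programme sets out to reduce medication. When insulin is withdrawn, the injected part leaves the measurement and HOMA-B drops for that reason alone. If withdrawal is more frequent in the intervention group, a between-group HOMA-B difference would partly reflect prescribing. At stake is any published statement about insulin resistance or beta-cell function, not the trial's main result.

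**Working it through.** The plan gives no HOMA figure to reproduce. The check is a sensitivity calculation on stated assumptions.

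**Inputs**

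- From the protocol article: insulin users are eligible; medication is tapered in the intervention group; standard formulas are used; there is no exception by treatment.
- Assumed, because not given: the usual closed forms, with glucose G in mg/dl and insulin I in uU/mL; own insulin 8 uU/mL; G = 130 mg/dl; injected insulin detected by the assay 0 to 12 uU/mL; share of insulin users 5% to 30%.

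**Formulas**

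HOMA-IR = G × I / 405

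HOMA-B = 360 × I / (G − 63)

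At fixed glucose both are proportional to measured insulin.

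**Step 1. One participant, own insulin and glucose fixed**

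| Injected insulin detected | Measured I | HOMA-B = 360 × I / 67 | HOMA-IR = 130 × I / 405 |
|---|---|---|---|
| 0 | 8 | 43.0 | 2.57 |
| 4 | 12 | 64.5 | 3.85 |
| 8 | 16 | 86.0 | 5.14 |
| 12 | 20 | 107.5 | 6.42 |

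Own secretion is the same in every row, yet HOMA-B ranges from 43.0 to 107.5.

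**Step 2. Does the result depend on holding glucose fixed?**

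Take measured insulin falling from 20 to 12 (detected injected insulin from 12 to 4).

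- Glucose stays at 130: HOMA-IR goes from 6.42 to 3.85 and HOMA-B from 107.5 to 64.5. Each falls 40%.
- Glucose rises to 200: HOMA-IR = 200 × 12 / 405 = 5.93, a fall of about 8%. HOMA-B = 360 × 12 / 137 = 31.5, a larger fall than before.
- HOMA-IR does not fall at all once glucose reaches 130 × 20 / 12 = 217.

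So the HOMA-IR movement depends on what glucose does. The HOMA-B fall remains if glucose holds or rises.

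**Step 3. If glucose improves as insulin is withdrawn**

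Let detected injected insulin go from 8 to 0 and glucose from 130 to 110, with own insulin still 8.

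- On own insulin, HOMA-B goes from 43.0 to 360 × 8 / 47 = 61.3, a rise of 43%.
- On measured insulin, it goes from 86.0 to 61.3, a fall of 29%.

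The index can therefore change sign in an insulin user who is doing better.

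**Step 4. Effect on a group mean**

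At 130 mg/dl, the mean HOMA-B shift when the injected part is withdrawn in all users is share × 360 × injected / 67.

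- Low end: 0.05 × 360 × 4 / 67 = 1.1
- High end: 0.30 × 360 × 12 / 67 = 19.3

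The range is wide because none of its inputs is stated.

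**The case against.** The strongest reply is that the article does not say who enters the HOMA analysis. It is a condensed document, and a fuller plan may restrict the set. Fasting insulin is collected only where a report happens to contain it, and the article does not name it as the HOMA input. HOMA is absent from the objectives, the outcome list and the statistical analyses, so there is no stated comparison to go wrong.

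Much of this stands, and it limits the point in several ways:

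- A reader might infer that the indices will be computed in every participant. The text supports only those with a fasting insulin result, and that fasting insulin is the input is itself inferred from the formulas and the test list. Availability does not screen out insulin users, however.
- A reader might infer that stopping insulin lowers HOMA-IR by 40% with no physiological change. That holds only if glucose stays at 130 mg/dl. Holding the same glucose on less circulating insulin may itself reflect lower resistance, and if glucose rises to 200 mg/dl the fall is about 8%.
- A reader might infer that a mechanistic group comparison is wrong for both indices. No such comparison is specified, and only the HOMA-B part is firm.
- A different distortion by group is an inference. The tapering text says medication, not insulin specifically, and dose handling in the control group is not described.

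What does not stand is treating this as mere silence. The Biochemical subsection fixes both the calculation and its interpretation, in a population where that interpretation fails for an identifiable subgroup.

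**Conclusion.** The point holds for insulin users. Followed as written, the plan would report as beta-cell function an index that can include injected insulin, and the programme is likely to change that component. HOMA-IR in the same participants is not interpretable in the usual way, but no direction should be claimed for it. The change may differ by group.

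The size cannot be fixed from the article: the share of insulin users, their insulin levels, the assay and the timing of injection are not given. Under the assumptions shown, the mean HOMA-B shift in a group runs from about 1 to about 19, that is, from negligible to large.

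Weight loss of at least 10%, remission and the listed secondary outcomes do not use HOMA and are unaffected. This is an inexpensive correction that should be made, not a threat to the trial's main conclusions.

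**What to change.** In the Biochemical subsection, or in the analysis plan if one exists:

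1. Name the input to each index and define the main HOMA analysis as participants not using insulin at baseline. Choosing the set on a baseline characteristic avoids selecting on treatment that the intervention itself changes.
2. For baseline insulin users, and for any sample taken after insulin is started during follow-up, do not use insulin-based HOMA. Report C-peptide, or a HOMA version validated for C-peptide input, where it is available. C-peptide cannot simply be put into the closed forms above, because units and constants differ.
3. Report by group how many participants contribute to each analysis, how many have no fasting insulin or C-peptide result, and how many lost an insulin-based value because insulin was started.
4. Give the analysis restricted to participants not using insulin at both compared visits only as a sensitivity analysis, and say that it selects on post-baseline treatment.

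This changes analysis wording only; no new test, visit or treatment change is needed. The price is a smaller HOMA set and incomplete C-peptide data, since C-peptide is also collected only where reports contain it.
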